### 2.2.12 Resource Utilization and Costs

Rising health care costs and limited health care resources have increased the focus placed on the economic aspects of health care. Analyses of resource utilization and costs contribute to decisions made by health service providers and policy makers regarding diabetes care. By incorporating measures of resource utilization, cost, and an intervention's effectiveness, cost-effectiveness analysis has become an important tool in decision making about the use of different treatments for the same condition. Several large trials of diabetes care interventions have demonstrated that enhanced treatment of diabetes improves health at an acceptable cost [DCCT Research Group 1996; Gary et al. 2000; Rodby et al. 1996].

Another secondary outcome of TODAY is an investigation of the resources, related costs, and cost-effectiveness of the three treatment arms. Resource utilization for each of the treatment arms is assessed throughout the trial and considers the intensity of services used in providing care and assuring adherence to each treatment regimen. The frequency of contact with physicians, nurse educators, psychological support staff, dietitians, and the use of drugs, equipment, and supplies are captured through study forms. Information on the time in which each of these health professionals is involved in treatment provision is obtained through surveys completed periodically by the providers.

The provision of care to youth and adolescents affects not just the study participants but also their caregivers. Participant and caregiver burdens may differ for each treatment. To consider this impact, several additional items that incur costs are assessed, including those of school absenteeism, work absenteeism (in children and adults), and the time spent in treatment activities by children and caregivers. These items are measured at baseline and periodically thereafter through surveys utilizing previously validated questions. We also assess academic and employment participation rates and progress since these outcomes may differ among treatment arms. Measurement of quality-adjusted life years is obtained through the HUI-2 (Health Utilities Index) [Furlong et al., 2001], which provides a preference-based measure of quality of life. The HUI-2 is administered at baseline, 6 months, annually, primary endpoint, and end of study.

The cost-effectiveness analysis considers the resources used and associated costs for each treatment arm throughout the time of the trial. The time frame of the analysis is short-term. The main analysis is based on the primary glycemia outcome in the trial and, thus, examines the costs of each treatment relative to the glycemia benefits obtained. By incorporating costs incurred by participants and caregivers, the analysis adopts a societal perspective, following the accepted standard for such studies [Gold et al. 1996; Drummond et al. 1999].

### 2.2.13 Gene Expression

The role that gene expression plays in the pathophysiology of type 2 diabetes, insulin resistant states, and long-term cardiovascular risk is not well-understood. The cohort of adolescents with type 2 diabetes provides a unique opportunity to establish a resource for exploration of gene-phenotype- outcome relationships. After randomization, we request that participants provide a blood sample for DNA that will be used for future studies of candidate genes for type 2 diabetes, obesity, insulin resistance, and cardiovascular complications of insulin resistance. A separate consent/assent is signed for donation of a DNA sample and refusal does not affect participation in the remainder of the TODAY protocol.

### 2.2.14 Pregnancy Outcomes

Few data have been reported on pregnancies in this demographic, including both the course of the pregnancy and the neonatal experience as well as outcomes for the mother and the baby. The importance of collecting data goes beyond the need to monitor and document safety in a clinical trial of experimental interventions.

Girls who become pregnant during TODAY are asked to participate in a separate data collection including pre-pregnancy history, care received during pregnancy, complications during the pregnancy, delivery data and perinatal complications. Participants sign a separate informed consent form and a medical release form so that the study can obtain relevant medical records and extract data.

## 3 Recruitment, Screening, and Enrollment

### 3.1 Recruitment Goals and Strategies

The primary source of participants for the TODAY study is the active patient population of the study sites and their usual referral sources. Supplemental strategies for increasing referrals (such as presentations to local physician groups) are also utilized. Site-specific recruitment strategies are developed by each local study team. The period of recruitment is anticipated to last four years.

The TODAY sites were chosen partially based on the ethnic/racial composition of their patients with T2DM. It is estimated that the ethnic/racial distribution of enrolled participants will be 33% African American, 31% Hispanic (largely Mexican American), 12% Native American, 20% non-Hispanic White, and 4% other (largely Asian American). Study sites will develop targeted strategies for maximizing the recruitment of the particular racial and ethnic groups seen in clinic.

Recruitment efforts are integrated into and supported by other TODAY activities, including national and local public relations efforts, on-going development and adaptation of recruitment and advertising materials, and presentations at local and national meetings. Recruitment of current patients as well as community-based recruitment will begin in parallel from the start of the enrollment period.

Recruitment progress is monitored regularly by the coordinating center and the Recruitment and Retention Committee. Limited, anonymous data are collected on individuals who refuse to participate in order to tailor the recruitment process. Assistance is offered to clinical centers struggling with recruitment efforts.

### 3.2 Screening Procedures

Screening for eligibility criteria involves completion of a screening visit and a 2-6 month run-in period. Screening proceeds from least invasive, most easily obtained criteria to the most demanding procedures. Once a patient is determined to be ineligible, the screening process stops.

If the patient is currently deemed ineligible but the patient's condition changes within the recruitment period (e.g., the patient has uncontrolled hypertension that can be treated), the patient may be reconsidered for inclusion if he/she maintains eligibility for three months. Screening procedures are re-initiated and the patient must meet all eligibility criteria at the time of enrollment.

A minimal amount of data are recorded on patients who fail screening (age group, gender, race/ethnicity, duration of diagnosis) for purposes of reporting progress to the NIDDK and for comparing participants versus nonparticipants.

### 3.2.1 Staged Screening

The staged screening process is intended to accomplish the following:

- identify potentially eligible patients for TODAY,
- verify eligibility of patients,
- accomplish the objectives of the informed consent process,
- complete a run-in period,
- establish a research cohort likely to complete the study and adhere to the protocol, and
- randomize patients into TODAY.

The staged screening process is a series of steps to evaluate the eligibility of children with T2DM, assess whether patients can safely tolerate metformin treatment, demonstrate adherence to medication taking and record keeping, and provide standard diabetes education (SDE) for all patients (see section below). Patients complete a run-in period to explore their ability to participate, ensure that they can achieve glycemic control and tolerate metformin, and sign a final informed assent/consent for randomization. Complete definitions and procedures are in the Manual of Procedures.

- *Initial Contact:* Identified patients are seen in clinic and are given detailed information about TODAY, including research interventions, randomization, masking, test procedures, risks and benefits, and the eligibility process. If they consent/assent, they are first interviewed and records reviewed for personal and medical history. If they pass these completely noninvasive eligibility criteria, then they continue to be evaluated.
- *Eligibility for Run-in:* Eligibility criteria requiring procedures, tests, and measurements are collected.
- *Run-in:* The run-in period (described in detail in section 4.1) is designed to (1) get the child on the maximum tolerable dose of metformin (no more than 1000 mg bid, no less than 500 mg bid), (2) wean all other diabetic medications, and (3) present a standard diabetes education program.  
 It also allows patients and their families to make an informed decision about participation in the study. Participants complete tasks similar to those required of study patients (e.g., taking pills on the correct schedule, completing nutrition and activity diaries, and keeping appointments).  
 The run-in period allows staff to evaluate a patient's suitability for TODAY. At the end of the run-in, clinic staff assess the patient's adherence to study tasks, assess final eligibility criteria, and determine whether the patient should be randomized to TODAY.
- *Randomization Visit:* If the patient is eligible, final informed assent/consent is obtained and the child is randomly assigned to a treatment group at this visit. Preparations to collect detailed baseline information are scheduled.

### 3.2.2 Informed Consent and Assent

The TODAY informed consent process occurs in stages in order to (1) maximize potential participant and family understanding of the TODAY study; (2) allow an informed decision regarding participation, including personal risks and benefits; and (3) promote the

efficiency of study procedures. This process is designed to meet the ethical obligations to the patient and improve retention by fostering a progressively increasing understanding of TODAY by the patient and family as well as the development of a positive relationship with the clinic staff. It is an interactive, conversational process, with the ultimate goal of maximum understanding of TODAY and its impact on the family, including the responsibility of the patient to TODAY and the responsibility of the investigators to the patient. It is anticipated that one result of this process is maximized retention of participants in TODAY.

All stages in the informed consent/assent process include provision of information in verbal and written form and the opportunity for discussion and questions. Each stage allows the participant to make a decision whether to proceed to the next phase of screening. After the presentation and discussion, the participant and family member are asked to sign the assent/consent forms relevant to that stage.

### 3.2.3 Eligibility Criteria Prior to Run-in

#### *Inclusion:*

1. Diabetes by ADA criteria (laboratory determinations of fasting glucose  $\geq 126$  mg/dL, random glucose  $\geq 200$  mg/dL, or two-hour OGTT glucose  $\geq 200$  mg/dL) documented and confirmed in medical record. For asymptomatic patients diagnosed with diabetes with a normal fasting glucose but an elevated two-hour glucose during an OGTT, the HbA1c must be  $\geq 6\%$ . For patients previously diagnosed with diabetes and on medication at the time of screening for eligibility, a laboratory determination of HbA1c  $\geq 8\%$  at the time of diagnosis will be accepted as surrogate evidence of eligibility, if there was no documented laboratory determination of serum glucose.
2. Duration since diagnosis less than two years by date of randomization.
3. BMI  $\geq 85^{\text{th}}$  percentile documented at time of diagnosis or at screening.
4. Fasting C-peptide at screening (drawn at least one week after treatment for ketosis or acidosis, if applicable)  $> 0.6$  ng/mL.
5. Absence of pancreatic autoimmunity (both GAD and ICA512 negative).
6. Age 10-17, with randomization prior to the 18th birthday.
7. Signed informed consent/assent forms for the pre-randomization period.
8. A family member or adult closely involved in the daily activities of the child agrees to participate in the child's treatment.
9. Fluency in English or Spanish for both child and family member.
10. Patient and family able to fully participate in trial protocol in the opinion of the investigator.

#### *Exclusion:*

11. Participating in another interventional research study protocol in the past 30 days.
12. Genetic syndrome or disorder known to affect glucose tolerance other than diabetes.
13. Patient on inhaled steroids at dose above 1000 mcg daily Flovent equivalent.
14. Patient on a course of oral steroids within the last 60 days or on oral steroids more than 20 days during the past year.
15. Patient on medication(s) that are known to affect insulin sensitivity or secretion within the last 30 days.
16. Patient on medication(s) that are known to cause weight gain within the last 30 days.
17. Patient on any weight-loss medication(s) within the last 30 days.
18. Patient on medication(s) known to affect the metabolism of study drug.
19. Inability to comprehend the lowest grade level at which lifestyle intervention materials are prepared, for both child and participating family member.

20. Females who are pregnant, planning to become pregnant within two years of enrollment, or who admit sexual activity without appropriate contraception.
21. Calculated creatinine clearance < 70 mL/min.
22. Any transaminase > 2.5 ULN. If any transaminase 1.5-2.5 times ULN, then patient must be appropriately evaluated (minimum evaluation includes ceruloplasmin level, alpha-1 antitrypsin phenotype, ANA, anti-smooth muscle antibody, anti-LKM antibody, anti-HCV, and anti-HBc total antibody not IgM, iron, and TIBC) and is eligible if all causes for transaminase elevation (other than NAFLD) are ruled out, and it is presumed that the elevation is due only to non-alcoholic fatty liver disease (NAFLD).
23. DKA at any time after diagnosis unless only a single episode of DKA related to a significant medical illness.
24. Physical limitations preventing patient from being randomized to the lifestyle intervention.
25. Patient plans to leave the geographic area within one calendar year.
26. Abnormal reticulocyte count or HbA1c chromatogram indicating the presence of abnormal hemoglobin variants other than heterozygosity for S and C at time of screening. Patients homozygous for S, C or S/C are excluded.
27. Admitted use of anabolic steroids within the past 60 days.
28. Other significant organ system illness or condition (including psychiatric or developmental disorder) that would prevent participation in the opinion of the investigator.
29. Patient participates in a formal weight-loss program.

#### 3.2.4 Eligibility Criteria After Run-in Prior to Randomization

The list includes criteria confirming protocol adherence during run-in as well as re-confirmation of some eligibility criteria from the first screening.

##### *Inclusion:*

1. Duration since diagnosis less than 2 years at randomization.
2. HbA1c < 8% on metformin alone.
3. Age 10-17, with randomization before patient is 18 years old.
4. Signed consent/assent forms for randomization and the post-randomization phase.
5. A family member or adult closely involved in the daily activities of the child agrees to participate in the child's treatment.
6. Fluency in English or Spanish for both child and family member.
7. Patient and family able to fully participate in trial protocol in the opinion of the investigator.

##### *Exclusion:*

8. Refractory hypertension: average systolic blood pressure  $\geq$  150 mmHg or average diastolic blood pressure  $\geq$  95 mmHg despite appropriate medical therapy.
9. Refractory hyperlipidemia: total cholesterol > 300 mg/dL or LDL > 190 mg/dL or triglycerides > 800 mg/dL, despite appropriate medical therapy.
10. Refractory anemia: hematocrit < 30% or hemoglobin < 10 gm/dL despite appropriate medical therapy.
11. Patient on a TZD within the last 12 weeks.
12. Patient on non-study diabetes medications within the past 6 weeks.
13. Patient on inhaled steroids at dose above 1000 mcg daily Flovent equivalent.
14. Patient on a course of oral steroids within the last 60 days or on oral steroids more than 20 days during the past year.

15. Patient on medication(s) that are known to affect insulin sensitivity or secretion within the last 30 days.
16. Patient on medication(s) that are known to cause weight gain within the last 30 days.
17. Patient on any weight-loss medication(s) within the last 30 days.
18. Patient on medication(s) known to affect the metabolism of study drug.
19. Inability to comprehend the lowest grade level at which lifestyle intervention materials are prepared, for both child and participating family member, assessed by mastery of standard diabetes education program administered during run-in.
20. Inability to comply with requirements of study during run-in period.
21. Females who are pregnant, planning to become pregnant within two years of enrollment, or who admit sexual activity without appropriate contraception.
22. Calculated creatinine clearance < 70 mL/min.
23. Any transaminase > 2.5 ULN. If any transaminase 1.5-2.5 times ULN, then the subject must be appropriately evaluated, if not already done (see Section 3.2.3, Exclusion #22) and is eligible for randomization if all causes for transaminase elevation (other than NAFLD) are ruled out and it is presumed that the elevation is due only to non-alcoholic fatty liver disease (NAFLD).
24. Physical limitations preventing patient from being randomized to the lifestyle intervention.
25. Patient plans to leave the geographic area within one calendar year.
26. Admitted use of anabolic steroids within 60 days.
27. Other significant organ system illness or condition (including psychiatric or developmental disorder) that would prevent participation in the opinion of the investigator.
28. Patient participates in a formal weight loss program.
29. Episode of DKA during the run-in.
30. Edema at the time of randomization (a participant who experiences edema during run-in must have recovered within 2 weeks and be edema free for 1 week prior to randomization).

### 3.3 Randomization

Randomization is stratified by clinical center to ensure balance among the treatment groups with respect to anticipated differences in the participant populations.

For each clinical center, the CoC generates a 1:1:1 randomization scheme using a permuted block design. Sample sizes across the three treatment arms remain relatively equivalent as the trial progresses, but the next treatment assignment cannot be anticipated.

The clinical center coordinator uses a computer-based system to input eligibility data and receive a random treatment assignment.

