- Urine ketones are measured as indicated if BG > 300 mg/dL.
- Serum creatinine is used to calculate creatinine clearance.
- If transaminases > 1.5 ULN, safety protocol is followed.
- Other anthropometric measurements are waist circumference and abdominal height.
- Screening lipid values are LDL and TG for determining eligibility. Other lipid assays include free fatty acids, lipoprotein subclass levels, average LDL particle density, and total ApoB levels.
- A comprehensive physical exam including Tanner stage and evaluation of acanthosis nigricans is performed at screening, baseline, all annual visits, and outcome. Otherwise a targeted physical exam is performed (every 2 months in year 1 follow-up and then quarterly).
- The FFQ is used for nutrition, 3-day PDPAR and 7-day recorded accelerometer for physical activity, and PWC 170 for fitness.
- The psychosocial and quality of life battery includes CDI, BDI, EDEQ (and QEWP-R if participant has high score on the EDEQ), PEDS QL, and HUI-2.
- Cardiovascular risk factors include measurement of fibrinogen, c-reactive protein, homocysteine (vitamin B-12 will be obtained to assess homocysteine), plasminogen activator inhibitor-1, interleukin-6. Pro-inflammatory and hemostasis markers are assayed at baseline, 6 months, 12 months, and end of study; blood from other draws is stored.
- Participants are asked about adverse events (AE) at clinic visits, but AE and SAE (serious adverse events) may be reported by the patient at any time.
- Data collected from the biological parent at baseline are height, weight, BDI, and EDEQ (and QEWP-R depending on EDEQ high score).
- Survey data include BDI, EDEQ (and QEWP-R depending on EDEQ high score), PEDS QL (adult proxy) and CHQ (P28).
- Data are collected every 2 months during the first year and quarterly thereafter from clinic staff on time spent for patient treatment. Logbook data are collected from clinic

staff every four months to further assess time spent providing treatment. Data are collected from patients and families regarding time and resource use related to treatment at baseline, 6 months, annually, primary endpoint, and at study closeout.

(p) The last HbA1c value during run-in is considered the baseline HbA1c.

(q) A sample of blood for DNA may be collected any one time after randomization.

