## 8.2 Statistical Analysis

The principal analyses of primary and secondary outcomes employ the "intent-to-treat" approach [Peduzzi et al. 1993]. The intent-to-treat analyses include all randomized patients with all patients included in their randomly assigned treatment group; treatment group assignment is not altered based on the patient's adherence to the assigned treatment regimen. All statistical tests are two-sided with the overall significance level of the primary outcome  $\alpha$

$\alpha = 0.05$ . However, b

TODAY, the significance levels used in the interim and final analyses of the primary outcome are adjusted to account for the multiplicity of interim analyses.

- *Baseline characteristics:* Comparison of the baseline characteristics among the three treatment groups uses standard nonparametric statistical techniques, such as Fisher's exact test for categorical data and the Kruskal-Wallis test for ordinal or continuous data.
- *Primary outcome:* The principal analysis of TODAY is an analysis of the time to treatment failure. Turnbull's [1976] algorithm is used to calculate and compare Peto's [1973] nonparametric estimates of the interval-censored survival curves for each treatment group. For the primary outcome analysis, patients are considered "administratively censored" if they complete the full duration of TODAY without having failed. Patients who prematurely discontinue their follow-up visits without having reached study endpoint are "censored" as of their last follow-up visit. Failure is considered to have occurred during the interval between the last HbA1c value  $< 8\%$  and the first HbA1c value used to classify the participant as a treatment failure.
- *Secondary outcomes:* Secondary time to "event" outcomes (e.g., cardiovascular risk factors, microvascular outcomes) are analyzed using the same life-table methods described above for the primary outcome. A proportional-hazards regression model is used to evaluate potential covariates that may modify the primary and secondary time to

event outcomes (e.g., risk population defined by race/ethnicity, age, clinical site). Graphical procedures are used to assess the proportionality assumption. If the proportionality assumption is found to be unreasonable, then other models such as the accelerated failure time model [Wei 1992] or the proportional odds model [McCullagh 1980] are used to evaluate the covariates.

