Life-table analysis assesses the risk of the first event in time. Some processes, however, involve recurrent events such as the back-and-forth between elevated and normal blood pressure. For these recurrent events, the family of statistical models based on the theory of counting processes are applied [Fleming and Harrington 1991].

Longitudinal data analysis techniques are used to analyze repeated measures data (e.g., glycemia, fasting lipids, blood pressure, physical activity, quality of life). These include: (1) analyses of the point prevalence of a discrete characteristic (e.g., hypertension) at successive repeated visits over time [Lachin and Wei 1988]; (2) multivariate rank analyses of quantitative (e.g., 2 hour OGTT) or ordinal (e.g., the Child Health Questionnaire subscales) measures over successive visits [Wei and Lachin 1984]; (3) the parametric linear random effects model of Laird and Ware [1982] to compare participant slopes over time (e.g., rate of change in fasting glucose) under linearity and normality assumptions; and (4) techniques developed by Liang and Zeger [1986] to compare participant slopes under a generalized linear models framework.

- *Interim analysis:* The Lan-DeMets [1983] spending function approach is used to adjust the probability of a type I error for testing the primary outcome when interim ‘looks’ of the data are taken by the Data Safety Monitoring Board. The spending function corresponding to an O’Brien and Fleming [1979] boundary are used. The Lan-DeMets procedure is flexible, in that the number of looks does not have to be specified in advance and the time interval between looks does not have to be the same throughout TODAY. The rate at which the type I error is spent is a function of the fraction of total information available at the time of the interim analysis (i.e., information time). For an interim analysis using the logrank test (i.e., time to confirmed treatment failure), the information time is the fraction of the total number of confirmed treatment failures to be accrued in the entire TODAY. Since the total number of failures to be accrued is unknown, an estimate of the information time is based on the fraction of total patient exposure [Lan and Lachin 1990].

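### The stated primary comparison uses neither the randomization stratum (clinical center) nor baseline HbA1c; the test is valid, but power is given up if baseline HbA1c is prognostic

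*Protocol*

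**What the plan says.** - **Randomization (Protocol 3.3).** "Randomization is stratified by clinical center to ensure balance among the treatment groups with respect to anticipated differences in the participant populations". Also: "For each clinical center, the CoC generates a 1:1:1 randomization scheme using a permuted block design". Center is the only stratification factor.
- **Primary analysis (Protocol 8.2, Primary outcome).** "Turnbull's [1976] algorithm is used to calculate and compare Peto's [1973] nonparametric estimates of the interval-censored survival curves for each treatment group". No strata or covariates are named.
- **Interim looks (Protocol 8.2, Interim analysis).** The information-time rule is given "For an interim analysis using the logrank test (i.e., time to confirmed treatment failure"), again with no strata.
- **Covariate modelling (Protocol 8.2, Secondary outcomes).** "A proportional-hazards regression model is used to evaluate potential covariates that may modify the primary and secondary" time-to-event outcomes. The examples given are race/ethnicity, age and clinical site. Baseline HbA1c is not among them.
- **Baseline HbA1c (Protocol 5.1, note p).** "The last HbA1c value during run-in is considered the baseline HbA1c".
- **Outcome and entry range.** Section 2.1 defines failure mainly as HbA1c at or above 8% over six months. Section 3.2.4 requires HbA1c below 8% on metformin alone at randomization.

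**The concern.** The outcome is a threshold crossing of a variable measured just before randomization. A participant who enters slightly below 8% is plausibly closer to failure than one who enters near the 6% treatment goal. If so, that difference is noise in an unadjusted comparison, and a covariate that eligibility already requires goes unused in the primary test. Center was judged important enough to stratify on, because the populations were expected to differ, yet it has no role in the primary test.

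What is at stake is power at the Bonferroni level of 0.05/3 per pair. The planned margin above 90% is not large.

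**Working it through.** **1. Inputs from the protocol (sections 1.2, 3.1, 8.1).** 250 per arm; two-sided 0.05 with Bonferroni for three pairs, so 0.01667 each (z = 2.394); 10% v 5%, or 20% v 12%, failing per six months; 10% dropout per six months; at least two years of follow-up; accrual of three years (1.2) or four (3.1); failures counted from the first annual visit.

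**2. The protocol's own power figure.** Yearly hazard = -ln(1-p)/0.5. The hazard ratios are:

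- ln(0.95)/ln(0.90) = 0.487
- ln(0.88)/ln(0.80) = 0.573

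The simple ratios of the six-month rates are 0.50 and 0.60. Expected events D come from exponential failure and dropout with uniform accrual. Power = Φ(√(D/4)·|ln HR| - 2.394). Example: D = 218.3 and HR 0.573 give 7.388 × 0.557 - 2.394 = 1.72, which is 95.7%.

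| Failures start | Accrual | D (10% v 5% / 20% v 12%) | Power | Power with HR 0.50 / 0.60 |
|---|---|---|---|---|
| month 6 | 3 y | 122 / 218 | 94.4% / 95.7% | 92.5% / 91.6% |
| month 12 | 4 y | 108 / 192 | 91.0% / 92.8% | 88.6% / 87.4% |
| month 12 | 3 y | 98 / 180 | 88.0% / 91.0% | 85.2% / 84.9% |

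The stated figure of at least 90% is reproduced under standard readings. The strictest readings fall somewhat short.

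**3. Effect of using center and baseline HbA1c.** Two-arm simulation: 250 per arm, 15 centers, permuted blocks, dropout as above, hazard from month 9, three-year accrual, 1,000 runs per setting (Monte Carlo SE about 1 point). The reference-arm two-year risk was held at its design value. The SDs of the log-hazard for HbA1c and center are **assumptions**; the protocol gives none. Each cell shows conditional HR 0.50 with the 10% rate / conditional HR 0.60 with the 20% rate.

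*Center only:*

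| Center SD | Unstratified logrank | Center-stratified logrank | Change (points) |
|---|---|---|---|
| 0.3 | 86.8% / 86.6% | 85.5% / 84.8% | -1.3 / -1.8 |
| 0.6 | 83.6% / 81.7% | 85.4% / 85.2% | +1.8 / +3.5 |

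*Center SD 0.3 plus baseline HbA1c:*

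| HbA1c SD | Unadjusted logrank | Stratified and adjusted Cox | Gain (points) | Unadjusted HR |
|---|---|---|---|---|
| 0 | 86.8% / 86.6% | 85.4% / 84.5% | -1.4 / -2.1 | 0.50 / 0.61 |
| 0.5 | 83.5% / 80.7% | 85.3% / 84.7% | 1.8 / 4.0 | 0.52 / 0.63 |
| 0.75 | 80.1% / 72.2% | 85.2% / 84.3% | 5.1 / 12.1 | 0.54 / 0.66 |
| 1.0 | 73.8% / 62.4% | 85.2% / 83.9% | 11.4 / 21.5 | 0.56 / 0.69 |

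The first row shows the cost if HbA1c is uninformative. It comes from stratifying, since the stratified logrank alone gives 85.5% / 84.8%; adding HbA1c costs at most 0.3 points.

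**4. If the design hazard ratio is read as marginal.** At HbA1c SD 0.75, conditional HRs of 0.46 / 0.54 give unadjusted HRs of 0.50 / 0.60. Power is then 87.9% / 88.2% unadjusted and 92.0% / 95.6% adjusted, a gain of 4.1 / 7.4 points.

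**5. Type I error.** With no treatment effect and HbA1c SD 0.75, rejection at nominal 1.67% is 1.2% / 1.6% unadjusted and 1.4% / 2.1% adjusted. Omitting the factors does not inflate it.

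**The case against.** **Strata and covariates often belong in the analysis plan, which is not shown.** This stands in part: that plan may add them, and section 3.3 gives balance as the purpose of stratification without promising a stratified analysis. But section 8.2 does fix the primary method by name, so the point concerns what is stated.

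**Clinical site is already modelled, and the covariate list is only illustrative.** True: the regression covers the primary outcome too, and baseline HbA1c is not excluded. But it explores covariates that may modify outcomes, and it sits apart from the principal comparison.

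**The magnitude rests on assumed effects.** This stands. The entry limit below 8% narrows the baseline range and may weaken its prognostic value.

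**A model-based test has costs.** This also stands. The hazard ratio becomes conditional and relies on proportional hazards. Lifestyle contact falls from weekly to quarterly (section 4.4.4), so a non-constant effect is plausible. The simulation used Cox models, whereas section 8.2 treats failure times as interval-censored.

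**Stronger readings that a reader might infer:**

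- *The unadjusted analysis biases the effect toward no difference.* Not supported. The unadjusted hazard ratio nearer 1 reflects non-collapsibility: it is a marginal quantity, and the marginal survival curves remain valid estimates.
- *Ignoring the strata makes the test invalid.* Not supported. Null rejection did not exceed the nominal level.
- *The planned power is wrong.* Not supported. It is reproduced under standard readings.

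**Conclusion.** The point holds as an efficiency recommendation, between optional and should-do. The stated primary comparison and interim logrank leave out the only randomization stratum and the most direct baseline measure of the outcome.

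The gain in power comes almost entirely from HbA1c: about 2-4, 5-12 or 11-22 points at assumed log-hazard SDs of 0.5, 0.75 or 1.0, and possibly at the low end given the truncated entry range. A reader might credit center stratification with a power gain of its own. The figures do not support that unless centers differ strongly: it changes power by about -2 to +4 points, and its main justification is consistency with the design.

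Confidence is high on what the text says and moderate on the size.

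**What to change.** Pre-specify that the primary pairwise treatment test, at interim and final looks alike, is stratified by clinical center and adjusted for last run-in HbA1c as a continuous covariate. One option is the treatment test from a center-stratified proportional-hazards or interval-censored model. Pool small centers by a rule fixed before unblinding.

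Keep the Turnbull/Peto curves as the marginal display and report the unadjusted comparison as a sensitivity analysis. State that the model's hazard ratio is conditional, and apply to it the proportionality check that section 8.2 already plans.

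The cost is protocol or analysis-plan wording. No new data are needed, since HbA1c at the end of run-in is required for eligibility. If HbA1c proves uninformative, the simulated price is about 1-2 power points, which comes from the stratification.
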